##### Concealment mechanism {16b}

In this study, the management method of “random center” is adopted. The random numbers were generated by the staff in charge of project (random center) statistics of Shanghai University of Traditional Chinese Medicine using the SAS software. The heads of clinical research centers, diagnostic intervention physicians, researchers, and participants of symptom and sign clinical data collection are unaware of the random numbers and corresponding groups.

##### Allocation and implementation {16c}

Upon participant enrollment, the diagnostic intervention physician is responsible for asking the person in charge of each participating clinical center for the random number and corresponding group information, and then the person in charge of each participating clinical center immediately asks for the random number and corresponding group code from the “random center” by telephone, and then the person in charge of each clinical center informs the patient of the random number, corresponding group code, and intervention measures by telephone or WeChat. The intervention physician shall not disclose the above information to the subject and the symptom and sign information collection physician.

#### Assignment of interventions: blinding

##### Blind implementation {17a}

The random grouping and intervention plan information is a blind setting for subjects and data statistical analysts. Blinding process: the blinding process is carried out in accordance with the blinding operation specifications of single-blind clinical trial drugs, and a blinding process record file is formed; the blind bottom storage adopts a 2-level blind method: the first level is the code corresponding to two treatment groups (randomly designated as a and b), and the second level is the code corresponding to each code. The two levels of blind bottom are sealed separately, each in duplicate, and stored in the Institute of Orthopedics and Traumatology by full-time personnel (not directly involved in the research work of this project).

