### Interventions

#### Intervention description {11a}

##### Trial group

The main intervention method in the trial group is Shi’s cervical manipulation therapy. The manipulation treatment team is composed of six clinicians (two in each of the three trial centers) with a minimum of 5 years’ experience in manual operation, who are good at manual spine diagnosis and treatment and have received standard operating procedures (SOP) training in this study. Each selected subject should have a 3-dimensional (3D) computed tomography (CT) reconstruction of the cervical vertebra, as well as a special physical examination of the cervical vertebra. Each subject will receive an initial diagnosis for 15–20 min after entering the group, including brief history collection, cervical static palpation (tenderness point and muscle spasm), cervical dynamic palpation (intervertebral looseness of the cervical spine), cervical sequence activity inspection, and cervical nerve reflex. Both history and examination results should be recorded in the case report form. According to the examination results, manipulation clinicians will give a comprehensive diagnostic analysis and manipulation therapy to each subject’s cervical spine. Key points of manipulation therapy operation are as follows: (1) acupoint pressing analgesia operation, according to the treatment principle of local acupoint selection and remote acupoint selection of cervical vertebra; point rubbing; and pressing operation are performed on the thumb pulp. The pressure can be light to heavy, then heavy to light, and the operation is repeated. The specific strength is to press until thumb nail color is white, while considering patient tolerance. Each acupoint is operated for 1 min. The specific acupoints are as follows: (a) local acupoints—Fengchi (International acupoint code GB20), Fengfu (International acupoint code DU16), Tianzhu (International acupoint code Bl10), Wangu (International acupoint code GB12), Dazhui (International acupoint code DU14), Jianjing (International acupoint code GB21), Jianzhongshu (International acupoint code SI15), Quepen (International acupoint code ST12), Tianzong (International acupoint code Si11), and Ashi; (b) remote acupoints—Lieque (International acupoint code LU7), Houxi (International acupoint code SI3), and Hegu (International acupoint code LI4). (2) Bone-setting manipulation operation, according to the results of palpation and 3D CT reconstruction of the patient’s cervical spine, the clinicians will give directional and fixed-point bone-setting manipulation to treat the cervical vertebrae semidislocation. The specific operation is as follows: the patient sits on the treatment chair, with the head slightly bent forward, and the manual operation physician stands at the patient’s side, with the right side as the patient’s side, for example, the manual operation physician locks his left thumb against vertebral plate between the transverse process and the spinous process of the cervical vertebra with semidislocation, and the other four fingers stick to the patient’s left head and neck, and the middle and upper part of the elbow of the right arm slightly bent on the patient’s lower jaw, according to the vertebrae semidislocation direction, the left thumb with pushing force to the vertebral plate in the opposite direction of semidislocation, while the right forearm rotates rapidly to lift and rotate the head with a direction- and size-controlled flashing force. There is a sliding motion and snapping sound from the vertebra under the left thumb. The whole manual operation treatment lasts for 20 min each time, and is done twice a week, with the longest course of treatment lasting for 12 weeks.

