
##### Control group

The main intervention method in the trial group is oral NSAIDs. Each selected subject should have a 3D CT reconstruction of the cervical vertebra, as well as a special physical examination of the cervical vertebra. The treatment team is composed of three clinicians (one in each of the three trial centers) with the qualification of clinical medical registered doctors and senior professional titles, who have received SOP training in this study. After exclusion of the contraindications of diclofenac sodium (known to be allergic to other components of diclofenac sodium, acetylsalicylic acid, ibuprofen, and Daphne, gastric and duodenal ulcer, gastrointestinal inflammatory disease, black stool, or unknown blood history), the NSAID diclofenac sodium double-release enteric-coated capsules (Difene, manufacturer Temmler Ireland. Ltd.; 75 mg, once a day, once a time, oral) is the main intervention. Each subject will receive an initial diagnosis for 15–20 min after entering the group, including brief history collection, cervical static palpation (tenderness point and muscle spasm), cervical dynamic palpation (intervertebral looseness of the cervical spine), cervical sequence activity inspection, and cervical nerve reflex. Both history and examination results should be recorded in case report form. Each subject will obtain a patient log card, which shall be kept by the patients themselves (handed over to the physician in charge of the group at the end of the test), and will be used to record name, dose, time, discomfort, combined medication, and other information about the drug taken truthfully every day. The specific drug dosage shall be specified by the physician in charge of the group according to the drug use instructions, and the maximum duration of the medication shall be 12 weeks.

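### Participants are declared blind to their treatment, but manipulation against capsules with no sham or dummy cannot be masked, so the primary pain score and the other self-ratings are unblinded self-reports

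*Protocol article*

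**What the plan says.** **The claim.** Blind implementation {17a} says: "The random grouping and intervention plan information is a blind setting for subjects and data statistical analysts". It adds that "the blinding process is carried out in accordance with the blinding operation specifications of single-blind clinical trial drugs" and describes a two-level sealed code for the groups.

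**The treatments.** Under Trial group, the manipulation is described as follows: "The whole manual operation treatment lasts for 20 min each time, and is done twice a week". Under Control group, the treatment is a named diclofenac capsule: "75 mg, once a day, once a time, oral) is the main intervention". Each control patient keeps a log card that "will be used to record name, dose, time, discomfort, combined medication, and other information about the drug taken truthfully every day". Drug distribution and recovery adds that these patients are handed a drug supply and return the kit.

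**Who is told.** Allocation and implementation {16c} says that the person in charge of the centre "informs the patient of the random number, corresponding group code, and intervention measures by telephone or WeChat". The next sentence reads: "The intervention physician shall not disclose the above information to the subject", and it extends the ban to the physician who collects symptoms and signs. Concealment mechanism {16b} says that centre heads, intervention physicians and data collectors "are unaware of the random numbers and corresponding groups".

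**The outcomes.** Under Outcomes {12}, the participant marks NRS pain on a line and staff measure where the mark falls. NDI, SF-36 and satisfaction are also patient self-ratings.

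**The concern.** The blinding statement is a positive claim about participants. It is not a gap that a fuller protocol or an analysis plan could fill, because neither could make these participants blind. What it says is hidden includes the intervention plan itself, so concealing only a group letter would not make it true.

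For a self-rated outcome the participant is the assessor. Masking the person who measures the mark, or the analyst, does not protect the score. The hypothesis is that manipulation is superior in efficacy and satisfaction, and self-ratings of both are open to expectation. If the claim carries through to the report, readers will take the primary result as participant-blinded when a between-arm difference may include expectation and reporting effects. The limitations listed in the Discussion do not mention this.

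**Working it through.** The point is decided by comparing sections; no figure in the plan depends on it.

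**Step 1. Could a participant be unaware of the treatment?**

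| Feature | Trial group | Control group |
|---|---|---|
| What the participant experiences | Hands-on pressing and neck manipulation, 20 minutes, twice a week | Capsule taken by mouth |
| What the participant keeps | No drug log described | Daily log with drug name and dose; kit returned |
| Sham or dummy of the other treatment | None described | None described |

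Participants {26b} also has a physician explain all procedures before consent. A participant who knows what the trial involves and receives one of these treatments knows which one it is. The answer is no, and it does not depend on how {16c} is read.

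**Step 2. Which outcomes are affected?** NRS (primary), NDI, SF-36 and satisfaction are rated by the participant. Cervical mobility is measured with a phone program and is not a self-rating.

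**Step 3. Which blinding can stand?** Analysts are declared blind in {17a} and again in Data collection {18a}, and the coded groups support that. Data collectors, under {18a}, are not to seek knowledge of the allocation, which is weaker than being blind. Drug distribution and recovery has an observer take back the drug kit at follow-up visits. If that observer also collects outcomes, the allocation is visible to that person.

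**Step 4. Illustration of size.** The shifts and their direction (favouring manipulation) are assumptions; the documents give none.

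- Inputs: SDs of 1.70 and 1.65 and N = 120 per group (Sample size {14}); two-sided 5% level.
- SE = √((1.70² + 1.65²)/120) = √(5.6125/120) = 0.216.
- With no true difference and a reporting shift b, the probability of P < 0.05 is Φ(b/SE − 1.96) + Φ(−b/SE − 1.96).

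| Assumed shift b (NRS points) | b/SE | Probability of P < 0.05 |
|---|---|---|
| 0 | 0 | 5.0% |
| 0.1 | 0.46 | 7.5% |
| 0.2 | 0.92 | 15.2% |
| 0.3 | 1.39 | 28.4% |

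For scale, the planned difference is 2.08 − 1.50 = 0.58 points, so a shift of 0.3 is about half of it (0.3/0.58 = 0.52).

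**The case against.** **Blinding is not feasible here, and readers can see that.** Both parts are true. An unblinded comparison of manipulation with a drug is a legitimate design, and the study calls itself exploratory. A reader might infer that the absence of participant blinding is itself a design fault; the documents do not support that. The fault is the statement that participants are blind.

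**The clause about informing the patient may be a translation slip.** A reader might infer from {16c} that the centre head tells every patient the intervention. Yet the intervention physician starts the request, and the next sentence presumes that this physician has received the answer and must not pass it on. The clause may have been meant to say that the head reports back to the physician. The two sentences need reconciling, but they do not prove that patients are told in this way. Step 1 stands without them.

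**The concealment section is probably sound.** A reader might infer that {16b} contradicts {16c}, since centre heads are said to be unaware of the groups and then obtain the codes. But {16b} is the concealment item and reads naturally as ignorance before assignment, while {16c} starts at enrolment. Rewriting {16b} to list heads and physicians as knowing the allocation would damage a sound statement.

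**The false-positive rates do not measure the wording error.** This stands. They describe a bias that any unmasked comparison of these treatments could carry, and rewording {17a} leaves them unchanged. They show only why the label matters.

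**Conclusion.** The claim of participant blinding in {17a} is wrong as written. It cannot hold for manipulation against capsules when neither arm has a sham or dummy, and correcting it changes how the NRS, NDI, SF-36 and satisfaction results may be interpreted. This rests on the treatments as the text describes them; Figures 1 and 2 were not available for the check.

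The rates of 7.5%, 15% and 28% are illustrations under assumed shifts and are not estimates of this trial's error rate. No sample-size input or planned test depends on the blinding label. The blinding of analysts is not called into question. That of data collectors is a stated intention, still to be checked against the kit recovery.

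**What to change.** - **Blind implementation {17a}:** state that participants and treating clinicians are not blinded. Limit the blinding claim to the statistical analysts and keep the two-level group code for them; removing the whole procedure would take away what supports analyst blinding. Say that outcome collectors are intended to be unaware of allocation, as {18a} has it, after checking whether the observer who recovers the drug kit also collects outcomes.
- **Allocation and implementation {16c}:** reconcile the two sentences on who tells the participant the allocation.
- **Procedure for unblinding {17b}:** align the emergency-unblinding text, since sealed letters have little function when patient and clinician know the treatment. The two planned unblindings after data lock and after analysis fit the analyst code and can stay.
- **Concealment mechanism {16b}:** at most, add that it applies before assignment.
- **Discussion (limitations) and final report:** state that the self-reported outcomes are open-label and that a between-arm difference may include expectation and reporting effects.

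The cost is wording in these places plus one check of staff roles. Sample size, tests and data are unaffected. Taking the centre head out of data handling would go further: under {18a}, {19} and {5d} the head appoints the collectors and receives the case records, so that would be a change of roles and is not needed for this correction. Recruitment was due to end on 31 December 2020 and the trial in October 2021, so the practical effect is mainly on accurate reporting.

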
##### Safety evaluation index

During the test, we should observe whether there are adverse reactions and adverse events, and make records. If there are adverse events, such as adverse effects on patients’ consciousness, feeling, exercise, sleep, blood pressure, pulse, heart rate, respiration, and other normal physiological indicators, cervical fracture, skin damage, spinal cord and vertebral artery injury, gastrointestinal discomfort or ulcer, bleeding, and black stool, the occurrence of adverse reactions shall be recorded in detail on the case observation form, including the time, severity, duration, and treatment measures, and correlation with experimental treatment method shall be analyzed with comprehensive consideration of complications and combined treatment. In case of adverse reactions, the clinical observation physician can decide whether to stop the trial according to the patient condition. Patients who stop treatment due to adverse reactions should be tracked and investigated, and the results should be recorded in detail.

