##### Procedure for unblinding if needed {17b}

In this study, there are two unblinding provisions. The first unblinding is at the end of blind audit data locking, and the second unblinding is at the end of statistical analysis. According to the emergency unblinding regulations, when patients need to receive emergency treatment due to adverse events, and the emergency treatment is related to the actual situation of receiving the study drug, the project research leader and the project supervisor can decide to open the emergency unblinding and read the corresponding emergency letters. Researchers should fill in the corresponding records with the date, reason, and process of unblinding.

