#### Data collection, management, and analysis

##### Data collection {18a}

The data involved in this project mainly include random grouping data, clinical baseline data, intervention symptoms and signs change, follow-up data, and results of statistical analysis data.

The random grouping data shall be provided by the researcher in charge of the random grouping of the project (random center) of Shanghai University of Traditional Chinese Medicine, and only the person in charge of each clinical research center has the right to obtain the data.

All clinical research centers are responsible for the diagnosis and screening of clinical baseline data, and the physicians are responsible for recording and collecting the data.

The person in charge of each clinical research center shall arrange full-time data collection personnel to collect the intervention symptoms, signs, and follow-up data. They shall not actively know the random grouping, intervention plan, and other information.

Statistical analysis results data are collected and provided by the researcher in charge of data statistical analysis (statistical center) of Shanghai University of Traditional Chinese Medicine, who do not know the random grouping and clinical intervention information. After clinical trial completion, the personnel from the “statistical center” will go to each clinical research center to find the person in charge of each subcenter to coordinate and collect the case observation form, record the observation form in the database, and lock it under the supervision of the general research director of the project and the project supervisor (not directly involved in the project research).

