##### Data management {19}

Before the start of the project, a complete project research operation SOP, investigator manual, and case report form should be established, and work training and summary meetings should be held before the start of the project and in the middle of the project, with detailed training and explanation of the test scheme, research operation SOP, and investigator manual contents. The case observation director of each research center should be established, and the case study work micro should be established by the person in charge of each research center credit group: case observation doctors in charge of each center should take photos of collected cases in the working group of each center, and give them to the person in charge of the subcenter who should, on the day of receipt, upload the standardized filing of the collected case report form. Consequently, Shuguang Hospital, the responsible unit of the project, should assign a special case supervisor, who should establish a WeChat working group with the person in charge of each center, and the supervisor should spot check the case report form from each center at any time to fill in the specification. After the test, the researcher (statistical center) in charge of project data statistics and analysis, a full-time statistician of Shanghai University of Traditional Chinese Medicine, should collect the original data from the case report form of each subcenter, and under the supervision of the chief research director of the project and the project supervisor (not directly involved in the project research), the assistant should cooperate with two people to back up and input those case reports into an Excel form, mutually proofread and correct input errors, check the accuracy with the original data in the case report form, lock the data, and then conduct statistical analysis.

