#### Statistical methods

##### Statistical methods for primary and secondary outcomes {20a}

Statistical results and data analysis are the responsibility of the researcher (Statistics Center) in charge of statistics and data analysis for the entire project, and the patients are divided into the following data sets according to different situations.

Full analysis set refers to the ideal set of subjects as close as possible to the intentional analysis principle (mainly including all randomized subjects). The data set is obtained after the elimination of the smallest and reasonable method among all randomized subjects. To estimate the missing value of the main variable, the last observation carried forward (LOCF) method is used to carry forward the missing part of the test data. The number of subjects in each group who evaluate efficacy at the end point is consistent with that at the beginning of the test.

Per-protocol set, all patients who meet the trial protocol, who use 80–120% of drugs, have good compliance, do not use prohibited drugs during the trial, and complete the CRF requirements.

Safety analysis set, all cases are randomly divided into groups, at least one use of study drug, or receive manual treatment, and at least one follow-up record, constitute the safety analysis population of this study. Safety population is the main population for safety evaluation in this study.

The main variables and the comprehensive efficacy analysis are the full analysis set and the compliance scheme set, respectively; the demographic and other baseline characteristics are the full analysis set; the safety evaluation is the safety set.

For continuous variables, the number of cases, mean, standard deviation, median, and minimum and maximum values will be listed; for classified variables, the form of frequency table (frequency and percentage) will be listed. Baseline is defined as the last observation data before the first treatment.

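### The analyst is declared blind until the analysis ends, but the same statistical centre collects, enters and analyses the case forms, and the analysis-set rules cannot be applied without seeing the arm

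*Protocol article*

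**What the plan says.** **The claim.** Blind implementation {17a} states: "The random grouping and intervention plan information is a blind setting for subjects and data statistical analysts". It supports this with a two-level sealed code, with arms labelled a and b. Procedure for unblinding {17b} adds: "The first unblinding is at the end of blind audit data locking, and the second unblinding is at the end of statistical analysis". Data collection {18a} repeats that the statistical-centre researcher knows neither the allocation nor the treatment given.

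**The data flow.** In {18a}, staff of the statistical centre "will go to each clinical research center to find the person in charge of each subcenter to coordinate and collect the case observation form"; they then record the forms in the database and lock it. In Data management {19}, the researcher in charge of statistics and analysis "should collect the original data from the case report form of each subcenter". Entry, proofreading, a check against source, lock and analysis follow in one chain. In both sections the research director and a project supervisor from outside the project oversee this work.

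**The set rules.** Section {20a} limits the per-protocol set to patients "who use 80–120% of drugs, have good compliance, do not use prohibited drugs during the trial" who also complete the form requirements. The safety set requires "at least one use of study drug, or receive manual treatment", plus a follow-up record. The main variables are analysed on both the full and the per-protocol sets.

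**The concern.** An a/b code blinds an analyst only if nothing else in the analyst's hands shows which arm a patient is in. Here one arm takes capsules and the other receives hands-on manipulation, with no dummy. Exposure, adherence and event-attribution data therefore point to the arm. The centre described as blind is the one that handles the source forms and is responsible for the analysis for which the sets are formed.

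What is at stake is decisions that need judgement. The full analysis set allows a minimal, reasonable exclusion without saying what qualifies. The per-protocol set asks for good compliance, and no numeric adherence threshold is given for manipulation. The Rejection criteria add further grounds, such as deviation from the trial plan. If someone who can see arm and outcome together makes these decisions, the protection that {17a} offers the reader is absent. The article's stated aim is to show that manipulation is better, so that protection should be real.

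**Working it through.** No arithmetic applies, because the point concerns who holds which information. The check sets the sections side by side.

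1. **Who is blind, and until when?** The statistical analysts, to both allocation and intervention ({17a}, {18a}). The two unblindings come at data lock and at the end of analysis ({17b}).

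2. **Who handles the forms?** The statistical centre. Section {18a} names its personnel as collecting, recording and locking. Section {19} names the researcher in charge of analysis as the collector, with assistants doing the entry. The collector and the analyst are therefore the same unit, and in {19} the same role.

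3. **What do the forms carry?** The form itself is not reproduced. The article requires the case observation form, the document collected under {18a}, to hold details of adverse reactions (Safety evaluation index), where also "correlation with experimental treatment method shall be analyzed". Section {11d} requires it to hold the reasons for drop-out and poor compliance. Drug logs and drug-return records are described only for controls (Control group; Drug distribution and recovery).

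4. **What do the set rules need?**
   - Per-protocol: the percentage of drug used. Only controls have a study drug, so applying the rule separates the arms.
   - Safety: whether the patient used study drug or received manual treatment. These alternatives are the two arms.

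5. **Who applies the rules?** Section {20a} opens with the statistics centre's responsibility and, in the same sentence, says that patients are divided into the sets. No other body is named, and no step that masks treatment fields is described.

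Result: steps 2, 4 and 5 cannot hold together with step 1. Even with step 3 left aside because the form is not shown, the rules in step 4 reveal the arm to whoever applies them.

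**The case against.** The strongest reply is that an article condenses. The case report form, operating procedures and investigator manual are not shown, and masked extracts or a set-fixing procedure may be described there. Drug logs go to the treating physician and drug use goes on a separate registration form, so the collected form may show less than feared. Entry is done with two-person proofreading under outside supervision. The full analysis set carries the last observation forward and keeps the number assessed at the end equal to the number at the start, which leaves little room for exclusion. Selective per-protocol exclusion would show as disagreement between the two sets. Finally, the primary outcome is patient-marked pain and {16c} has the patient told the intervention, so analyst masking is a secondary safeguard.

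Much of this limits the size of the problem, but the contradiction remains. The article does not merely leave the data flow open: it assigns form collection to the analyst and gives set rules that need the arm. Supervision and double entry protect accuracy and do not mask treatment.

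Four stronger readings are tempting, and the text does not support them.
- **That the arm is seen before the sets are fixed.** Section {20a} gives no date, and {17b} mentions a blind audit at lock, where the sets might be fixed.
- **That all 240 records reveal the arm to the analyst.** Without the form this cannot be counted.
- **That the statistical centre supervises its own entry.** Supervision belongs to the research director and project supervisor.
- **That the bias can be sized.** Any figure depends on an assumed number of excluded patients. Suppose normal scores with the manipulation arm's planning SD of 1.70. Dropping the worst 5% shifts that arm's mean by about 1.70 × 0.103 / 0.95 = 0.18 points; dropping the worst 10% shifts it by about 1.70 × 0.175 / 0.90 = 0.33. The document favours neither, and both describe deliberate selection.

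**Conclusion.** The plan is wrong as written. It promises an analyst who does not know allocation or intervention until the analysis ends, and then describes a process in which the analyst's own centre collects the source forms and whose set rules reveal the arm. The sealed code does not deliver the stated blind.

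This rests on two things the article states: the analyst collects the forms, and the set rules depend on drug use or manual treatment. It also rests on one reading, that the statistics centre applies those rules, since {20a} names nobody else. It does not depend on the layout of the form or on any suspicion of misconduct.

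The consequence is a risk of unmasked judgement over membership of the full and, more plausibly, the per-protocol set. Its size cannot be derived from the document. The point should be corrected before data lock. It does not by itself undermine the trial.

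**What to change.** In {18a}, {19} and {20a}:

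1. Have the existing entry assistants collect and enter the forms, on the stated condition that they neither hold the randomisation list nor take part in the analysis. The data manager in {16a} stores that list and should not take this role, because allocation and outcomes would then be in the same hands. For the same reason, exclude the assistants who {15} says are in charge of patient grouping.
2. Fix the full, per-protocol and safety set flags at the blind audit, before lock, from exposure and adherence records with outcomes hidden. People other than the analyst should do this and document it.
3. Release to the analyst only outcomes, the a/b code and the flags. Hold back drug, session and event-attribution fields until the week-12 pain analysis is complete.

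If this is not done, delete the statistical analysts from the blinded parties in {17a} and remove the matching statement in {18a}.

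The cost is protocol wording and a reassignment of existing roles. The downside is that the safety and adherence tables come slightly later than the efficacy results.
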